### Distal outcomes

In this RCT, we refer to distal outcomes as continued improvements in functioning and symptom outcomes, measured at 3-, 6-, and 12-month follow-ups, extending beyond the 6-week intervention phase. Distal outcomes of interest include changes in anxiety (GAD-7) and depression (PHQ-9) symptom severity, PA and NA (PANAS), anhedonia (DARS), ER (ERQ), and reward sensitivity (PVSS). Other distal outcome measures are summarized in Table 1. Assessing distal outcomes is crucial to determining how immediate treatment gains translate to long-term therapeutic benefits. They also offer insights into how the Digital PAI may cultivate long-term changes in behavioral, cognitive, and emotional processes linked to common mental disorders. Studying distal outcomes is also integral to assessing dose-response effects, relapse patterns, and the broader effects of treatment type and skill usage on everyday functioning. It also concurs with recommendations for DMHIs to move beyond assessing short-term gains and evaluate ecological validity across lengthy time horizons [110, 111]. The 12-month long-term follow-up helps to address such knowledge gaps in the sustainability of DMHIs.

### Data management

All study data will be entered directly by the participants into both Qualtrics and the mEMA Ilumivu app, which are HIPAA-compliant software that use encrypted servers to maintain private and secure data transmission and storage. Data integrity will be routinely monitored through periodic data quality checks conducted by the PI ([name]), as well as trained and supervised research assistants (RAs) and study coordinators. These procedures consist of cross-checks among research personnel to detect and resolve inconsistencies. Backups of the most up-to-date data sets from both Qualtrics and mEMA will be performed monthly and securely stored on institutional servers in line with university data protection guidelines and cloud computing policies.

### Auditing and internal oversight

No independent data monitoring committee is planned, given the low-risk nature of this RCT, which the NUS institutional review board (IRB) approved under the Human Biomedical Research Act (HBRA). However, internal oversight processes and safeguards are in place: trained and supervised RAs perform all baseline data collection visits in pairs, with the PI purposefully absent to minimize bias. Research personnel routinely audit the database to ensure study protocol fidelity and the timely implementation of follow-up assessments. In addition, participants who endorse a score of 2 or 3 on the PHQ-9 item 9 (self-harm or suicide ideation) during the screening survey trigger a standard suicide risk assessment [112] and safety planning procedures, including identifying reasons for living and providing clinical referral resources, conducted by trained research personnel. Adverse events (AEs) and serious adverse events (SAEs) will be tracked and reported via the same protocols for suicidality screening and monitoring, i.e., administration of the PHQ-9 and the Columbia-Suicide Severity Rating Scale [C-SSRS; 112]. These tools aid in systematically detecting and documenting AEs/SAEs, and any cases reaching criteria will be recorded per IRB rules.

### Statistical analysis plan

#### Data processing and missing data management

All preprocessing steps and data analyses will be conducted using the *R* software [113]. Using an intention-to-treat (ITT) approach, we will estimate between-group treatment efficacy for continuous and binary clinical outcomes [114]. A complier average causal effects (CACE) analysis will also be conducted to determine treatment efficacy between high- and low-potential engagers [115]. Before conducting the key data analyses, a series of preprocessing steps will be undertaken. These include anomaly diagnostics, assumption checks (e.g., linearity, multivariate normality), and random forest imputation of missing data. Random forest imputation with the *missRanger* package [116] will be used instead of multiple imputation because it better handles nonlinear associations and interactions and generates improved performance even under missing not-at-random (MNAR) conditions [117]. Sensitivity analyses will be conducted by examining outcomes under two alternative missing data management approaches, full information maximum likelihood (FIML) and multiple imputation [118]. The point estimates and 95% confidence intervals (CIs) of all effect sizes, Cohen’s *d* for continuous outcomes [119], as well as odds ratios [ORs] and risk ratios [RRs] for binary outcomes [120], will also be computed consistently.

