### Sample size and power

The *R* package *simr* [56] was used for power calculations, which simulated a multilevel model with time and group as fixed effects. The primary outcomes are anxiety and depressive symptoms, indexed by GAD-7 and PHQ-9 scores, respectively. Given the low-intensity nature of the Digital PAI and its evaluation against a Self-Monitoring Placebo as a placebo control [57], we expected the between-treatment effect sizes to range from small (Cohen’s *d* = 0.2) [26, 58] to moderate (*d* = 0.5) [24]. To achieve a statistical power of 81% while detecting small to moderate between-group efficacy effect sizes at a 5% significance level, a sample size of between 300 and 1,600 is required. Accounting for an estimated 50% attrition rate, our planned sample size was 1,200 (600 participants per group).

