### Daily self-monitoring placebo control

Self-Monitoring Placebo participants receive a fully automated delivery of EMA prompts thrice daily (morning, afternoon, and evening) over the 6-week timeframe from baseline. Unlike the Digital PAI group, the Self-Monitoring Placebo does not consist of any psychotherapy content, skills-building practices, or treatment elements. Participants instead complete brief mood-monitoring self-reports designed to measure dynamic daily variations in emotional states. These EMAs include ratings on affective changes, current mood, emotional valence (positive, neutral, or negative), emotional preparedness, and the impact of daily events (e.g., activities, social interactions) on mood. Systematic variations in the EMA prompt content are introduced to minimize habituation (response set acquisition) and response burden while also sustaining participant engagement. This assessment-only method is used to adjust for nonspecific factors, such as attention, expectancy, and recurrent mood monitoring, thus enabling a strict validation test of the distinctive therapeutic effects of Digital PAI.

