### Protocol adherence and engagement strategies

Participants will receive three Digital PAI or Self-Monitoring Placebo prompts per day across 6 weeks, totaling 126 prompts. Protocol adherence is operationally defined as the completion of at least 80% of these prompts (i.e., ≥ 101 of 126 prompts). Non-adherence is defined as missing key assessment batteries at baseline, mid-intervention, or post-intervention, or completing < 80% of all prompts. Beyond pro-rating reimbursement, other engagement strategies included giving automated reminders to participants and embedding brief 1 to 3-minute pre-recorded videos of the PI outlining the rationale of the Digital PAI techniques at the start of each section. Interactive components are also embedded in the weekly Digital PAI sessions, allowing participants assigned to the treatment group to engage in hands-on activities while learning the therapy content. Participants may withdraw from the study at any time without providing a reason and will not be required to complete any additional procedures.

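### The CACE analysis is given the task of comparing high with low engagers, but a complier effect describes one stratum only and, in its standard form, carries no information on that contrast

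*Protocol article*

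**What the plan says.** The statistical analysis plan section, under data processing and missing data management, first sets the main approach: "Using an intention-to-treat (ITT) approach, we will estimate between-group treatment efficacy for continuous and binary clinical outcomes". It then adds one sentence on engagement: "A complier average causal effects (CACE) analysis will also be conducted to determine treatment efficacy between high- and low-potential engagers". No estimator, identifying assumption or separate low-engager effect is named; the method is left to a citation.

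Three other places bear on it.

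- The section on the daily self-monitoring control says that "the Self-Monitoring Placebo does not consist of any psychotherapy content, skills-building practices, or treatment elements". Control participants therefore have no described access to the PAI, and non-compliance is one-sided.
- The section on protocol adherence and engagement strategies gives the only engagement cut-off in the document: "Protocol adherence is operationally defined as the completion of at least 80% of these prompts (i.e., ≥ 101 of 126 prompts". It does not mention the CACE.
- The same section adds: "Non-adherence is defined as missing key assessment batteries at baseline, mid-intervention, or post-intervention, or completing < 80% of all prompts".

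**The concern.** The stated purpose is a comparison: does the PAI work differently in people inclined to engage a lot and people inclined to engage little? The method named for it estimates a single quantity, the effect in those who would comply if offered the PAI. With one-sided non-compliance, the textbook CACE is identified by assuming that assignment does nothing for non-compliers. The low-engager effect is then an input to the analysis and not a result of it.

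At stake is the interpretation. A CACE reported under the stated purpose would look like evidence that efficacy is concentrated in high engagers, even if both groups benefit equally or low engagers benefit more. This is a mismatch of method and purpose in the text as it stands, so it differs from a technical detail that an article may leave to a fuller plan.

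**Working it through.** The document gives no figure for this analysis, so there is none to reproduce.

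**Inputs**

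- Expected effects, from the sample size section: 0.2 to 0.5 SD.
- Arm size, from the same section: 600 per group; after 50% attrition, 600 × (1 − 0.5) = 300 per group.
- Share of high engagers, p: not given. Assumed 0.3, 0.5 and 0.8.
- Control arm: no PAI content, so the strata are would-be engagers and never-engagers.

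**Step 1: what the data identify.** Let E_high and E_low be the effects of assignment in the two strata.

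ITT = p × E_high + (1 − p) × E_low

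This is one equation with two unknowns. The exclusion restriction sets E_low = 0, which gives CACE = ITT / p. Substituting the true ITT shows what is actually reported:

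CACE = E_high + [(1 − p) / p] × E_low

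Any benefit in low engagers is added to the figure reported for high engagers.

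**Step 2: different truths, same CACE (p = 0.5, effects in SD)**

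| E_high | E_low | True contrast | ITT | CACE = ITT / 0.5 |
|---|---|---|---|---|
| 0.2 | 0.2 | 0 | 0.20 | 0.40 |
| 0.4 | 0 | +0.4 | 0.20 | 0.40 |
| 0 | 0.4 | −0.4 | 0.20 | 0.40 |
| 0.2 | 0.4 | −0.2 | 0.30 | 0.60 |
| 0 | 0 | 0 | 0 | 0 |

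The first three rows cannot be told apart. In the fourth, low engagers gain more, yet the CACE rises.

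**Step 3: check by simulation.** There were 4,000 trials per row, with 600 per arm, residual SD 1, and engagers differing in prognosis by 0.5 SD. Mean CACEs were 0.40, 0.40, 0.40, 0.60 and 0.00, as the algebra gives. The interval excluded zero in 93%, 91%, 93%, over 99% and 5% of trials. At 300 per arm the first three rates were 67%, 65% and 66%. ITT power at 0.2 SD in a simple two-group comparison is 93% with 600 per arm and 69% with 300. Testing the CACE against zero is therefore close to testing the ITT effect again.

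**Step 4: range over p when both strata benefit equally (true contrast 0)**

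| Common effect | p = 0.3 | p = 0.5 | p = 0.8 |
|---|---|---|---|
| 0.2 SD | 0.2 / 0.3 = 0.67 | 0.40 | 0.25 |
| 0.5 SD | 0.5 / 0.3 = 1.67 | 1.00 | 0.63 |

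**Step 5: if the adherence cut-off were used as compliance (an assumption).** 0.8 × 126 = 100.8, so the cut-off is 101. Someone completing 100 PAI prompts would count as unaffected by assignment. So would someone who completed all 126 but missed the Week 3 battery. A zero effect is implausible for such people. With E_low = 0.2 SD, the inflation [(1 − p) / p] × 0.2 is 0.47, 0.20 and 0.05 SD at p = 0.3, 0.5 and 0.8.

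**The case against.** The strongest reply is that the exclusion restriction is not in the document. The wording about potential engagers also fits a principal-stratum method, such as one based on principal ignorability or a covariate-based mixture model, that estimates a non-zero effect in low engagers. The cited source cannot be checked here, and an estimator for a supplementary analysis is commonly left to the full plan. This stands, and it makes the point conditional. It does not remove it: the only method named is CACE, which by definition is the effect in compliers, and if another method is meant the sentence still needs correcting.

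Four stronger readings are tempting, and the documents do not support them.

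- A reader might infer that the plan fixes the low-engager effect at zero. It never says so; that belongs to the standard form of the method.
- A reader might infer that 101 of 126 prompts is the CACE compliance definition. That cut-off defines protocol adherence in both arms and is not linked to the CACE.
- A reader might take the simulated rejection rates as false-positive rates of the plan. They essentially reflect ITT power, and no test of CACE = 0 as a test of equal efficacy is specified.
- A reader might infer that the CACE would drive the dosing and dose-response conclusions mentioned under proximal and distal outcomes. Neither section refers to it, and who benefits most is addressed separately by the moderation analyses.

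It is also fair to say that a principal-score analysis replaces one untestable assumption with another.

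**Conclusion.** The point holds in conditional form. The CACE is assigned a comparison that it does not make. If it is identified by the exclusion restriction, it is ITT / p and is silent on whether high and low engagers differ: at p = 0.5, equal benefit, benefit only in high engagers and benefit only in low engagers all give 0.40 SD when the ITT effect is 0.20 SD. With equal true effects across the expected range of 0.2 to 0.5 SD, the reported high-engager figure would lie between 0.25 and 1.67 SD for p from 0.8 to 0.3, beside an assumed zero in low engagers.

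This rests on the standard identification, one-sided non-compliance and assumed engagement rates. The concern about inflation at the 80% cut-off additionally assumes that this cut-off would define compliance. The analysis is supplementary and the ITT conclusions are untouched, but the correction is worth making because it prevents a wrong statement about engagement.

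**What to change.** In the CACE sentence of the statistical analysis plan section:

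1. Describe the CACE as the effect of assignment to the PAI versus control among would-be engagers, and state the exclusion restriction.
2. Define compliance at a level of exposure below which no effect is plausible, for example no session opened and no EMI completed counting as non-compliant.
3. State that the CACE will not be used to compare high with low engagers.
4. If that contrast is wanted, name a method that estimates both stratum effects. One option is to predict PAI-arm engagement from baseline variables, apply the score to both arms and test the arm-by-predicted-engagement interaction. State its assumption that baseline variables explain engagement.

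The cost is a change of wording and a modest extra analysis of baseline data and app logs that are already being collected. Data collection is ongoing and the analyst is blinded until it ends, so this can be settled beforehand. The drawbacks are lower precision for the contrast and reliance on an assumption that cannot be verified.

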#### Statistical approaches for primary and secondary outcomes

Prospective analyses of primary and secondary continuous outcomes, such as anxiety and depressive symptom severity (GAD-7 and PHQ-9), anhedonia (DARS), and PA (PANAS), will be analyzed using multilevel modeling (MLM) with restricted maximum likelihood estimation (REML). Piecewise MLM will be used to assess between-group differences in changes across unique timeframes (e.g., baseline to post-treatment vs. post-treatment to 3-month follow-up), enabling the estimation of distinct linear slopes before and after critical time points to model nuanced changes in clinical outcomes over time. The MLM models will consist of fixed effects of group (Digital PAI vs. Self-Monitoring Placebo) and two-way group-by-time interaction to account for within-person associations. We will use the *nlme* package [121] for all analyses, assuming random intercepts and slopes for all models. Level 1 will model within-person changes over time, and Level 2 will capture between-person factors. All outcomes will be modeled across recurring time points (baseline, mid-treatment [Week 3], post-treatment [Week 6], as well as 3-month, 6-month, and 12-month follow-ups), aligned with this RCT’s assessment schedule. Covariates will include demographic variables (e.g., age, sex), baseline symptom severity, and device wear time, where relevant, for variables that significantly differed between groups at baseline. Between- and within-group effect sizes will be computed for all outcomes of interest [119, 122]. For binary clinical outcomes, such as depression remission indexed by PHQ-9 ≤ 4, generalized estimating equations (GEE) will be utilized to estimate between-group efficacy across all time points and follow-ups, accounting for repeated assessments with an exchangeable working correlation structure [123, 124]. Standard MLM with a logistic linking function will also be conducted as a sensitivity analysis for binary outcomes [125].

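### Primary missing-data method: random forest imputation pulls the raw arm difference towards zero if both arms are imputed together, and the article states no safeguard

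*Protocol article*

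**What the plan says.** Under Data processing and missing data management, imputation is part of the preparation of the data: "Before conducting the key data analyses, a series of preprocessing steps will be undertaken". The method and its rank are explicit: "Random forest imputation with the *missRanger* package [116] will be used instead of multiple imputation because it better handles nonlinear associations and interactions". The article adds that the method also performs better when data are missing not at random. The sensitivity analyses use "two alternative missing data management approaches, full information maximum likelihood (FIML) and multiple imputation".

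Under Sample size and power, the expected loss is large: "Accounting for an estimated 50% attrition rate, our planned sample size was 1,200 (600 participants per group"). The assumed effect is modest, from d = 0.2 to d = 0.5.

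Under Statistical approaches for primary and secondary outcomes, GAD-7 and PHQ-9 go into REML multilevel models over six time points. Remission is handled separately: "For binary clinical outcomes, such as depression remission indexed by PHQ-9 ≤ 4, generalized estimating equations (GEE) will be utilized".

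The article does not say whether the arms are imputed together or apart, which variables enter the forest, or whether predictive mean matching or repeated imputation is used.

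**The concern.** The stated reason for the choice concerns how well single missing values are predicted. A trial needs the filled-in values to preserve the difference between the arms, which is a separate property.

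In a forest, each split sees only a random subset of predictors. If group is one binary predictor among many, and its effect is small next to earlier symptom scores, few splits use it. Participants who drop out of either arm are then filled towards a common prediction. The ITT estimate becomes a mixture of the real difference in those observed and a weaker one in those imputed. This happens even when dropout is completely random, where analysis of the observed scores has no such bias.

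Two further faults follow. A single filled-in data set analysed as if observed ignores the uncertainty of the imputation. Forest predictions are also close to conditional means and have too little spread, so applying the cut at 4 to them can give wrong remission rates and hence wrong odds ratios and risk ratios.

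**Working it through.** **The plan's own figure.** Two-sided 5% and 81% power (two-sided is assumed; the article does not say):
- d = 0.2: n per arm = 2 × (1.960 + 0.878)² / 0.2² = 403, so 806 in total and 806 / 0.5 = 1,612 after 50% attrition. The article's upper end is 1,600.
- d = 0.5: 65 per arm, 130 in total, 260 after attrition, against a stated lower end of 300. The article used simulation with inputs it does not show.

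The article gives no figure for imputation bias.

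**Algebra.** Let m be the share missing and c the share of the true effect that the imputed values carry. Share of the raw difference retained = (1 − m) + m × c. At m = 0.5:
- c = 0: 0.50
- c = 0.25: 0.625
- c = 0.5: 0.75

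**Simulation of c.**
- From the article: N = 1,200, 1:1, d of 0.2 to 0.5, 50% attrition, and 12 repeated scales at 5 post-baseline visits (60 variables). Table 1 also lists 17 baseline-only instruments.
- Assumed: 25 further baseline variables in the full set, correlation 0.55 within a scale over time and 0.30 between scales, the same effect on all scales, and half the effect at Week 3.
- Forest: chained, 50 trees, √p candidate predictors per split, minimum node size 5. It is a reimplementation, not missRanger itself.
- Dropout is completely random. *Early* means all 50% lost before Week 3. *Staged* means 20%, 30%, 40%, 45% and 50% lost by the five visits.
- Estimator: baseline-adjusted group difference at one visit. Ratios are to the observed-case estimate in the same data (Week 6 / Month 12).

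| Variables | True d | Dropout | Arms | c | Raw difference retained | Cohen's d ratio |
|---|---|---|---|---|---|---|
| Full set | 0.2 | early | together | −0.02 / −0.03 | 0.50 / 0.49 | 0.56 / 0.53 |
| Full set | 0.5 | early | together | 0.10 / 0.08 | 0.55 / 0.55 | 0.64 / 0.62 |
| Full set | 0.3 | staged | together | 0.10 / 0.28 | 0.74 / 0.65 | 0.78 / 0.71 |
| Full set | 0.5 | staged | together | 0.20 / 0.36 | 0.77 / 0.69 | 0.82 / 0.78 |
| 12 scales only | 0.3 | early | together | 0.17 / 0.19 | 0.58 / 0.59 | 0.73 / 0.72 |
| GAD-7, PHQ-9 | 0.2 | early | together | 0.42 / 0.40 | 0.72 / 0.70 | 0.90 / 0.88 |
| GAD-7, PHQ-9 | 0.5 | early | together | 0.57 / 0.53 | 0.79 / 0.76 | 0.98 / 0.95 |
| GAD-7, PHQ-9 | 0.3 | staged | together | 0.67 / 0.60 | 0.90 / 0.80 | 1.01 / 0.98 |
| GAD-7, PHQ-9, matched | 0.3 | early | together | 0.32 / 0.39 | 0.66 / 0.70 | 0.66 / 0.69 |
| Full set | 0.3 | early | by arm | 1.05 / 1.01 | 1.03 / 1.01 | 1.28 / 1.23 |

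Group was a predictor in every run with the arms together. Leaving it out retained 0.49 to 0.50. The rows had 9 to 38 replicates, so ratios are good to roughly 0.05. The algebra agrees: full set, d = 0.5, early, Week 6 gives 0.5 + 0.5 × 0.10 = 0.55.

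A second simulation used 4 repeated scales, 26 baseline variables and lag-one correlation 0.65, with group in the forest. With 50% missing at Week 6 and Month 12, 0.5 became 0.32–0.33 and 0.2 became 0.11. With 15%, 30% and 50% missing at Week 3, Week 6 and Month 12, 0.5 became 0.41 at Week 6 and 0.37 at Month 12. Observed-data estimates were 0.49–0.51.

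**Standard error.** By arm, the model SE was 0.037–0.038, against 0.067–0.068 for observed cases. Treating 600 observed values as 1,200 alone gives 0.067 × √(600/1,200) = 0.047. The rest comes from the shrunken spread.

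**Remission, illustrative.** The second simulation assumed a mean of 7.5 and SD of 4.5 at Month 12 (not in the article) and d = 0.2. True rates of 25% and 32% became 17% and 20% after imputation. The odds ratio moves from (0.32/0.68)/(0.25/0.75) = 1.41 to (0.20/0.80)/(0.17/0.83) = 1.22.

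**The case against.** The strongest reply is that the size depends on settings the article leaves open. Table 1 is an assessment schedule, not an imputation model. A condensed article may leave pooling of arms, the variable set and matching to the full plan, and by-arm imputation shows no attenuation. The 50% is overall attrition, and the Discussion ties dropout particularly to the 12-month follow-up, so fewer scores may be missing at Week 6. Cohen's d, which the article will report, shrinks less than the raw difference. Neither missRanger nor the planned piecewise model with random slopes was run. FIML and multiple imputation are already planned and would expose a discrepancy.

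Most of this stands, and it makes the size conditional. It does not remove the point. The article does fix the method, its place before the models and its rank above the alternatives. No setting tried with one filled-in data set was sound: imputing the arms together attenuated the raw difference in every run, and imputing by arm left the SE too small and d inflated. A milder loss in d is one error partly masking another. Sensitivity analyses can reveal the disagreement, but the plan would still rank the affected estimate first.

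**Conclusion.** The point holds conditionally. If the arms are imputed together, the raw ITT difference is pulled towards zero under completely random dropout. The loss is about 25–50% with a Table 1-like variable set, depending on when dropout occurs. It is about 10–30% with only GAD-7, PHQ-9 and group unmatched, and 30–34% with matching. If the arms are imputed separately, the attenuation disappears, but the SE is too small (about 0.037 against 0.067) and Cohen's d is inflated by 1.23 to 1.28. Remission rates from unmatched predictions can be distorted either way. These sizes rest on the assumed correlations and the reimplemented forest.

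The documents do not support four stronger readings:
- **The effect is roughly halved, or the imputed values carry none of it.** That holds only for the full variable set with all dropout before Week 3.
- **The plan pools the arms.** It does not say.
- **Power is lost.** At d = 0.2 in the full set with early dropout, the test statistic at Week 6 was 0.095/0.038 = 2.5 after imputation and 0.189/0.067 = 2.8 on observed cases, because the smaller SE offsets much of the loss. The point concerns the estimate and its error.
- **The trial answers a different question.** The target is unchanged; what is at issue is bias in the estimator.

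**What to change.** - **Continuous outcomes.** Make the REML multilevel model, fitted to all observed GAD-7 and PHQ-9 scores without prior imputation, the primary ITT analysis. It is already the planned model, and it is valid when dropout is random given the data in the model.
- **Binary outcomes in the GEE.** Use proper multiple imputation, either by arm or with group and its interactions in the imputation model, and derive remission from the imputed scores.
- **missRanger.** Move it to a sensitivity analysis. If it is kept, run it by arm with predictive mean matching and repeated imputations pooled by Rubin's rules. A single imputation by arm is not enough.

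The cost is wording: the methods are already in the plan and mainly change rank. The primary analysis would no longer model nonlinear associations in the missing data, and its confidence intervals would be wider. Recruitment is under way, so the change should be recorded before the analyst is unblinded.

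### The primary analysis rests on what reads as a single random forest fill with no variance correction, so intervals are too narrow and type I error exceeds 5% by an amount the plan leaves open

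*Protocol article*

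**What the plan says.** Protocol article, Data processing and missing data management: "Before conducting the key data analyses, a series of preprocessing steps will be undertaken". The steps listed are anomaly diagnostics, assumption checks "and random forest imputation of missing data". No outcome or visit is exempted. The random forest method "will be used instead of multiple imputation because it better handles nonlinear associations and interactions", and a second reason given is better performance when data are missing not at random (MNAR). The same section adds: "Sensitivity analyses will be conducted by examining outcomes under two alternative missing data management approaches, full information maximum likelihood (FIML) and multiple imputation".

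Statistical approaches for primary and secondary outcomes: continuous outcomes go into a piecewise multilevel model fitted by REML, with random intercepts and slopes, over baseline, Weeks 3 and 6 and Months 3, 6 and 12. Binary outcomes such as PHQ-9 ≤ 4 go into GEE.

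Sample size and power: "Accounting for an estimated 50% attrition rate", the plan is 600 per arm. No visit is attached to the 50%.

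The article does not say whether arm enters the forest, whether each arm is filled separately, or whether predictive mean matching is used.

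**The concern.** A single completed data set carries no record of how uncertain the filled values are. A model fitted to it sees 600 people per arm at every visit, however many were lost. Two things go wrong with the variance. The sample is counted as larger than it is, and, without matching, the filled values are conditional means that lack residual scatter. Robust GEE errors do not help, because they also take filled values as data.

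If one forest is trained on both arms with arm as one predictor among many, the filled values also lean toward a common mean, which pulls the treatment effect toward zero. Conditional-mean fills can further move people across a cut-off such as PHQ-9 ≤ 4.

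At stake are the primary p-values, confidence intervals, effect sizes and remission rates, and the error grows with dropout. It is also avoidable: REML on the observed records is valid under missing at random (MAR) without filling the outcomes first.

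**Working it through.** **Inputs from the article.** 600 per arm; 5% significance (two-sided assumed); effect sizes d = 0.2 to 0.5; 50% attrition; six visits.

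**The plan's own figure.** It states that 300 to 1,600 are needed for 81% power. The two-sample formula gives, for d = 0.2, 2 × (1.960 + 0.878)² / 0.2² ≈ 403 per arm, 806 in total, and 806 / 0.5 = 1,612 after attrition, close to 1,600. For d = 0.5 it gives 65 per arm, 130 in total and 260 after attrition, not 300. The article's figures come from a simulation whose variance inputs are not shown, so this is only a rough match. What matters here is that 50% is a loss of participants, not the share of values missing at each visit.

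**Closed form, each arm filled separately.** Let p be the share missing at a visit, n the number per arm and σ² the residual variance after adjustment.

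- Conditional-mean fill: true variance of the arm mean is σ²/[(1−p)n]; the model reports (1−p)σ²/n. Ratio = 1/(1−p)².
- Random-draw fill: true variance is σ²/[(1−p)n] + pσ²/n; the model reports σ²/n. Ratio = 1/(1−p) + p.
- Type I error = 2[1 − Φ(1.96/√ratio)].

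| Share missing | Fill | Ratio | Type I error |
|---|---|---|---|
| 20% | conditional mean | 1.5625 | 11.7% |
| 20% | random draw | 1.45 | 10.4% |
| 50% | conditional mean | 4.0 | 32.7% |
| 50% | random draw | 2.5 | 21.5% |

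If the comparison is unadjusted and the predictors explain half the outcome variance, these fall to about 8% at 20% missing and to 17% and 14% at 50%.

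**Simulation.** Assumptions: 600 per arm, six visits, monotone dropout completely at random, observed shares 100, 85, 75, 65, 58 and 50%, outcome SD close to 1, six further covariates. There was one chained random forest fill (a Python forest, not missRanger itself), then ANCOVA of Month 12 on baseline and arm. Null settings had 400 replicates each.

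| Fill | Model SE | True SE | Type I error |
|---|---|---|---|
| Pooled, arm as predictor | 0.039 | 0.046 | 9.5% |
| Pooled, with matching | 0.048 | 0.052 | 7.2% |
| By arm | 0.039 | 0.078 | 33.8% |
| By arm, with matching | 0.048 | 0.071 | 19.5% |

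Observed data only (four runs): 4.3, 6.8, 4.8 and 3.0%, mean 4.7%; coverage 93-97%.

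Monte Carlo error on the 7.2% is √(0.072 × 0.928/400) = 1.3 points, so that row alone does not exclude 5%. Its model SE is still below its true SE, as in every setting.

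With a true effect of 0.2 (200-250 replicates), the pooled forest returned 0.15 with 75% coverage, or 0.17 with 84% coverage when matched. The by-arm forest without matching was nearly unbiased (0.196), but coverage was 68%.

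**The case against.** The strongest reply is that the size is not a property of the plan. That stands. A reader might infer that type I error is several times 5%. This holds for by-arm filling at 50% missing, but the pooled forest above gave only 1.4 to 2 times 5%. A simulation with 50% lost at Week 6 under MAR and fewer predictors gave 17-18% even with arm as a predictor, which shows how far the number moves with settings.

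A reader might also take half of all data to be missing, or half at Week 6. The article does not say so. Its Discussion ties dropout mainly to the 12-month follow-up, and randomization follows the baseline battery, so early visits should lose less.

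That the fill is done once is an inference, though a strong one: a forest fill that was repeated and pooled would itself be multiple imputation, which the article lists separately.

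None of the checks fitted the planned piecewise model or GEE. The direction should carry over; the exact percentages are not shown to.

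On MNAR, the article makes a comparative claim and cites a source that is not available here, so calling it false goes too far. It is still no reason for this choice, because prediction from observed values cannot identify dependence on unobserved ones. The lack of a named MNAR analysis is not a fault here, since that is commonly left to the statistical analysis plan.

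Finally, FIML and multiple imputation are prespecified, so a discrepancy would be visible. That limits the harm but does not repair the primary interval.

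**Conclusion.** The point holds in this form: the stated primary handling of missing data gives standard errors that are too small and type I error above 5%. At an assumed 50% missing at Month 12, the simulated single-visit ANCOVA puts type I error at about 7-10% for a pooled forest, with the effect shrunk and coverage 75-84%, and at about 20-34% for by-arm filling. By-arm filling at 20% missing gives about 10-12% in the closed form with adjustment. These figures rest on assumed correlations, an assumed dropout path, and dropout completely at random in the simulation.

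Distortion of threshold outcomes is a possibility if matching is not used. In the Week 6 simulation, remission fell from 19% to 10% without matching; no figure with matching is available, so a general bias in remission is not shown. Nor do the documents support ranking this as the largest threat to the trial, since no other threat was sized for comparison.

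This is not a detail left for later. The article states the choice and argues for it.

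**What to change.** 1. Continuous outcomes: make the REML multilevel model on all observed records primary, with no prior imputation of outcomes.
2. Binary outcomes: impute the scores by multiple imputation, by arm or with arm in the model (random forest with predictive mean matching is acceptable). Then derive the cut-offs, fit the GEE to each data set, and pool by Rubin's rules.
3. Move the single missRanger fill to sensitivity, or drop it for outcomes.
4. Remove performance under MNAR as the reason for choosing it.

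The cost is mostly wording, because FIML and multiple imputation are already listed and recruitment is still under way. Analysis work rises a little and intervals widen. In the simulation the observed-data model SE was 0.072-0.073 against 0.039-0.048 after a single fill, a factor of about 1.5 to 1.9. That compares a complete-case ANCOVA. REML and multiple imputation also use the earlier visits and may lose less, but neither was simulated.
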